### 2.4 Trial Statistics and Analysis

We do not yet have the information necessary for a formal power calculation. The aim of this study is to measure feasibility including estimating the effect size and standard deviation to formulate a power calculation for a definitive trial. The sample size of 30 in each arm would be able to detect an effect size of 0.8 in a continuous variable such as weight loss, and if allowing for a 20% attrition rate (n=16), 0.9. Therefore we do not expect do detect differences unless the effect size is large.

For the preliminary efficacy outcomes, between group and group*time interactions will be used to estimate the intervention effects (analysis of variance). The analysis will be performed using SPSS by intention to treat. Further regression analysis will be used to adjust for any potential confounding factors not factored into the stratification.

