**X = all participants**

**X = only participants randomised to intervention group**

**2.4 Outcome Measures**

The primary outcome is feasibility of the trial. This will be assessed during the process evaluation through:

- recruitment rate
- attrition rate
- reasons for non-acceptance
- trial procedures for randomisation
- amount of staff time required
- fidelity, measured through a self-report check-list
- staff feedback on feasibility
- participants’ satisfaction with the intervention
- acceptability of research procedures, data collection and overall experience of the trial

The secondary outcomes will assess preliminary efficacy of the intervention. We will measure the following :

- Oral Glucose Tolerance Test (OGTT) to assess differences ≥1 mmol/l in either fasting or two hour postprandial glucose
- Incident T2DM and a subsequent GDM pregnancy (NICE criteria)
- Relative and absolute weight loss at multiple time points considering the number of women achieving significant weight loss (>5%) at 3 and 9 months postpartum from a baseline of the booking appointment weight
- Lifestyle factors, following the Medical Research Council (2012) diet and physical activity measurement toolkit and from accelerometer
- Other metabolic and anthropometric factors will include HbA1c, waist circumference and blood pressure
- Psychological factors; depression/anxiety (PHQ9) and postnatal depression (Edinburgh postnatal depression scale)
- Health related quality of life- EuroQol EQ-5D-5L will be used to assess health related quality of life
- Diabetes risk perception (Risk Perception Survey for Developing Diabetes used in the DPP [9]).
- Infant factors- infant feeding intentions, breast feeding duration, weight gain and growth, and measure of attachment.
- Attitudes to body [23], eating behaviour [24] and motivation for dietary change [25].
- Additional data will include: age, ethnicity, deprivation, employment, education, pre-pregnancy BMI, parity, previous GDM and birth outcome data

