### 3. Sample Size, Selection and Withdrawal of Subjects

A convenience sample of 60 women with current GDM, 30 in each arm will be recruited. King’s College Hospital antenatal diabetes clinic sees around 200 new patients with GDM a year, equating to 17 a month, and Guy’s and St Thomas’ Hospitals see 700 (58 a month). Participants will be recruited opportunistically at their routine clinic appointment upon diagnosis of GDM, group education session the following week, or at a following clinic visit, by a diabetes nurse, consultant or dietician. We estimate that with a 30% recruitment rate we can recruit our sample within 3 months, or with a 15% recruitment rate we can recruit within 6 months. The intervention will last approximately 12 months (depending on gestational stage at diagnosis – usually this is around 28 weeks but can be earlier), with follow-up stopping at 9 months postpartum. We aim to start recruitment, ethical approval permitting, in March 2018, and finish data collection in September 2019. We expect the data to be analysed by December 2019.

Pregnant women have been chosen because: (1) previous research and our qualitative research indicates this is the best time to recruit women to start providing support, (2) women are already engaged with health services so may be easier to recruit, (3) women may be more receptive to behaviour change support during pregnancy, and (4) the highest cumulative incidence of T2DM after GDM is in the first 5 years postpartum, so any intervention should start as soon as possible after identification of GDM.

Potential participants will be identified by the clinical team working at KCH and GSTT. Potential participants will be given the participant information sheet explaining the purpose of the study. Participants who indicate a potential interest in the study will be given the opportunity to consider their participation in the study before being scanned by the researcher for full eligibility using the eligibility screening form. After screening, if the patient is eligible they will undergo consenting, either on the same day or another day at their convenience. Participants may withdraw their interest in the study at any point during the screening and consenting process and their details will not be stored.

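### The observed effect size from about 48 completers is named as an input to the definitive power calculation, but it is too imprecise for that use; the SD is not

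*Protocol*

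**What the plan says.** Section 2.4, Trial Statistics and Analysis, opens with "We do not yet have the information necessary for a formal power calculation" and then gives the purpose of the study as including "estimating the effect size and standard deviation to formulate a power calculation for a definitive trial". Both quantities are named as inputs to the next trial's sample size.

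The same paragraph gives the study's sensitivity: "The sample size of 30 in each arm would be able to detect an effect size of 0.8". The endpoint is left generic, with weight as the only example. A second figure then follows for the study after dropout: "if allowing for a 20% attrition rate (n=16), 0.9". The paragraph closes on a caveat: "Therefore we do not expect do detect differences unless the effect size is large". Section 3 fixes the size: "A convenience sample of 60 women with current GDM, 30 in each arm will be recruited".

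The Outcome Measures section names thresholds of interest. The glucose tolerance test is "to assess differences ≥1 mmol/l in either fasting or two hour postprandial glucose", and weight loss above 5% is counted. Neither threshold is linked to the sample size of a later trial. Nowhere does the protocol say that the target difference will be set on clinical grounds, or that a confidence limit will be used in place of the point estimate.

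**The concern.** A sample-size calculation for a comparison of means needs a target difference and an SD. A study of this size estimates the SD tolerably well but the difference poorly, and the required sample size varies with the inverse square of the difference. A chance high estimate therefore gives a definitive trial that is much too small, and a chance low one gives a trial that is far too large or cannot be sized at all.

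The protocol's caveat about detecting only large effects concerns significance testing in this study. It does not deal with carrying the same imprecise estimate forward as a planning value. This is also separate from the attrition figure printed in the same paragraph, which needs its own correction.

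**Working it through.** **Inputs.**
- 60 women, 30 per arm (section 3).
- 20% attrition (section 2.4): 60 × 0.20 = 12 lost, leaving 48, or 24 per arm. The printed n=16 does not match: 16 lost would leave 44. I use 24 per arm and check 22 and 30.
- Alpha, power and the true effect are not stated. Assumed: two-sided 5%, 80% power, and a true effect mainly of 0.3 to 0.5 SD.

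**The plan's own figures.** By the noncentral t, power is 86.1% at 0.8 SD with 30 per arm and 86.3% at 0.9 SD with 24 per arm. The stated 0.8 and 0.9 thus agree with each other at about 85% power if 24 per arm remain. With 16 per arm, power at 0.9 SD would be only 69%.

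**Precision of the effect size.** Unadjusted, SE ≈ √(2/24) = 0.289, so the half-width is 1.96 × 0.289 = 0.57 SD. An observed 0.4 SD has a 95% CI of about −0.17 to 0.97.

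**What that means for sizing.** n per arm = 2 × ((1.96 + 0.842)/d)².
- d = 0.4: 98.1, so 99 per arm.
- d = 0.97: 16.7, so 17 per arm.
- d = −0.17: no finite size.

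**Precision of the SD.** With 46 degrees of freedom the 95% CI is 0.83 to 1.26 times the estimate. Required n scales with the square, a factor of 0.69 to 1.58.

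**Direct entry of the point estimate.** In 400,000 simulated feasibility studies per setting, with 24 per arm, each positive estimate is put into the formula above. The resulting trial's power is then evaluated at the true effect.

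| True effect (SD) | Correct n per arm | Estimate ≤ 0 | True power < 50% | n within a factor of two |
|---|---|---|---|---|
| 0.3 | 175 | 15% | 33% | 28% |
| 0.4 | 99 | 8% | 28% | 37% |
| 0.5 | 63 | 4% | 24% | 45% |
| 0.8 | 25 | 0.3% | 14% | 64% |

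As a rough check, true power falls below 50% when the estimate exceeds the true effect by the factor (1.96 + 0.842)/1.96 = 1.43. At a true 0.4 SD that is an estimate above 0.572. P(Z > (0.572 − 0.4)/0.289) = P(Z > 0.595) ≈ 0.28.

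**Sensitivity at a true 0.4 SD (chance of true power below 50%).**
- Completers: 29% with 44, 28% with 48, 26% with all 60.
- Baseline adjustment in both trials: residual SD = √(1 − r²). With r = 0.7 the half-width is 0.57 × √0.51 = 0.40 SD and the chance is about 22%. With r = 0.9 the half-width is 0.57 × √0.19 = 0.25 SD and the chance is about 11%. The protocol gives no correlation, so both values of r are assumptions.

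**The case against.** The strongest reply is that the protocol says only that the effect size and SD will be estimated in order to formulate a power calculation. It does not say that the raw point estimate will be entered unaltered, and an analysis plan or the definitive trial's own protocol could set out a more careful use. That is fair, and it makes the simulation conditional on direct entry. It does not remove the point: the stated purpose puts the effect size beside the SD as an input, with no qualification.

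Second, the unadjusted figures are a worst case, because the protocol plans group-by-time analysis and regression adjustment. This also stands. Adjustment shrinks the problem, to 22% or 11% in the cases shown, without removing it.

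Third, the definitive endpoint is not yet fixed (weight loss is only an example), so a single target difference cannot be written down now. That limits how specific the fix can be, but the rule for setting the target can still be stated.

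A reader might also infer three stronger things that the document does not support:
- That the study cannot tell no effect from a large one. With 24 per arm, power is 77% at 0.8 SD and 86% at 0.9 SD, and an observed 0.8 SD has a 95% CI of 0.21 to 1.38. It is small and moderate effects that cannot be separated from none.
- That the effect size is the study's chief quantitative result. The Outcome Measures section makes feasibility primary, including recruitment, attrition and staff time, and treats efficacy as secondary and preliminary.
- That a low estimate would lead the sponsor to abandon the intervention. No section ties progression to the effect estimate.

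**Conclusion.** The concern holds for the effect size and not for the SD. With 44 to 60 women analysed, the observed effect is too imprecise to size the next trial. Entered directly, it would leave that trial with true power below 50% in roughly a quarter to a third of cases for true effects of 0.3 to 0.5 SD, without baseline adjustment. A strong baseline correlation would reduce this to about one case in five (r = 0.7) or one in nine (r = 0.9) at a true 0.4 SD.

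These figures rest on assumed alpha, power, true effect and correlation, and on direct use of the point estimate, which the protocol's wording invites but does not spell out. The defect does not bias this study's own results or its feasibility outcome. It affects the design of the trial that follows, and it should be corrected because the wrong use is written into the aim.

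**What to change.** In section 2.4, Trial Statistics and Analysis, replace the stated aim with wording to this effect:

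- The study will supply the SD, the baseline to follow-up correlation and the retention rate for the definitive power calculation.
- The target difference, for whichever endpoint is chosen, will be a minimum important difference justified independently of the effect observed here.
- The observed effect will be reported with its 95% CI, and used only to check that the target is not ruled out.

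Optionally, enter the SD at an upper confidence limit. The one-sided 80% limit with 46 degrees of freedom is 1.10 times the estimate (1.103² = 1.217), which raises the definitive sample size by about 22%. The choice of limit, and whether the target comes from the glucose or weight-loss threshold already named or from elsewhere, is for the sponsor.

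The cost is a few sentences. This study needs no extra participants, visits or measurements.

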### Study Synopsis

| **Title** | **G**estati**o**nal **D**iabetes future **D**iab**E**te**S** prevention **S**tudy – feasibility trial |
| --- | --- |
| **Protocol Short Title/Acronym** | GODDESS |
| **Protocol Version number and Date** | Version-4  Date: 17/01/18 |
| **Study Phase if not mentioned in title** | N/A |
| **Is the study a Pilot?** | No |
| **Study Hypothesis** | The primary hypothesis (H^O^1) for the study is that a lifestyle intervention to increase physical activity and promote weight loss in women with recent gestational diabetes mellitus (GDM) is feasible |
| **Study Duration** | 18 months |
| **Methodology** | Feasibility randomised controlled trial (RCT) |
| **Sponsor name** | [name] |
| **Chief Investigator** | [name] |
| **REC number** | **177238** |
| **Medical condition or disease under investigation** | Risk of type two diabetes in women with previous gestational diabetes |
| **Purpose of clinical trial** | To test the feasibility of a trial to improve diet, increase physical activity and promote weight loss in women with recent GDM, with a view to preventing or delaying T2DM |
| **Primary objective** | To explore the acceptability of a lifestyle intervention to increase physical activity and promote weight loss in women with recent GDM, and test the feasibility of the trial |
| **Secondary objective (s)** | To assess preliminary efficacy of the intervention |
| **Number of Subjects/Patients** | 60 |
| **Trial Design** | Feasibility two-armed parallel group RCT |
| **Endpoints** | Once the primary outcome variables have been appropriately measured and data analysis completed, this marks the end of the study. |
| **Main Inclusion Criteria** | - aged ≥18 years - diagnosed with GDM (NICE cirteria) - ≤30 weeks pregnant - able to speak and understand English - body mass index (BMI) of ≥ 25kg/m^2^ (or ≥22 kg/m^2^ if Asian) |
| **Statistical Methodology and Analysis** | Feasibility will be assessed through the process evaluation.  For the preliminary efficacy outcomes, between group and group*time interactions will be used to estimate the intervention effects (analysis of variance). The analysis will be performed using SPSS by intention to treat. Further regression analysis will be used to adjust for any potential confounding factors not factored into the stratification. |

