### 2.3 Trial Design & Flowchart

The study has been designed as a feasibility two-armed parallel group RCT with integrated process evaluation, as shown in the adapted CONSORT diagram in Figure 1. An RCT has been chosen because: (1) this is the gold standard design to determine causal associations, (2) a control group design is necessary because changes related to pregnancy and the postpartum period might impact outcomes (e.g. weight change) and make between group interactions less reliable than group*time interactions, and (3) the study will provide preliminary information on feasibility with regards to recruitment and retention, acceptability and outcome measures, before undertaking a large-scale RCT.

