**Figure 1. CONSORT flowchart**

**29-32 weeks' gestation:** Dietician or researcher provide information to potentially eligible participant during group education session. Or clinician providing routine care to approach potentially eligible participants at first clinic appointment - brief verbal and written information given and verbal permission for researcher to contact sought

**Baseline / randomisation visit (29-33 weeks' gestation):** Eligibility confirmed; written informed consent (if not previously obtained); randomisation; demography; questionnaires; anthropometry; blood pressure; blood sample; OGTT, provided with 7 day accelerometer and instructions

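### The ANOVA terms named as estimators of the intervention effect should give way to a baseline-adjusted model of the 3- and 9-month values

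*Protocol*

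**What the plan says.** Section 2.4 (Trial Statistics and Analysis) makes estimation of the effect size and SD for a later power calculation an aim of the study. For the preliminary efficacy outcomes it then says that "between group and group*time interactions will be used to estimate the intervention effects (analysis of variance"). The Study Synopsis repeats this, and both places add: "The analysis will be performed using SPSS by intention to treat". No SPSS procedure is named. A further regression is planned to adjust for confounders.

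Section 2.3 gives a control group as necessary because pregnancy and postpartum changes may "make between group interactions less reliable than group*time interactions".

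There are three measurement occasions: the "Baseline / randomisation visit (29-33 weeks' gestation"), then 3 and 9 months postpartum. The reference value differs by outcome. Weight loss is assessed "at 3 and 9 months postpartum from a baseline of the booking appointment weight" (section 2.4, Outcome Measures). Section 4.2 takes the baseline OGTT from the patient record. Sections 3.3 and 4.1 say that data collected before withdrawal are kept and analysed unless the woman objects, and section 4.1 says that none are collected afterwards.

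On size: "A convenience sample of 60 women with current GDM, 30 in each arm will be recruited". Section 2.4 (Trial Statistics and Analysis) takes weight loss as its example outcome and puts the detectable effect at 0.8 SD with 30 women per arm. Its figure after drop-out is given as: "if allowing for a 20% attrition rate (n=16), 0.9".

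**The concern.** Two different terms are offered as the estimate of the intervention effect, and the protocol does not say which one goes forward to the definitive trial.

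A between-group main effect averages the arm difference over every level of time. If baseline is one of those levels, the average includes a visit at which randomisation makes the expected difference zero. The group*time term avoids this, but with three visits it tests a pattern on 2 df and gives no single mean difference.

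Section 2.3 prefers group*time without a condition, although the preference holds only when the visits are correlated strongly enough. A classical repeated-measures ANOVA also needs complete data on every visit, which fits poorly with intention to treat and with the undertaking to use data collected before withdrawal.

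At stake is the effect size used to plan the next trial. If an effect shrunk to two thirds were paired with a single-visit SD, the planned sample size would grow by (3/2)² = 2.25.

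**Working it through.** **Inputs from the protocol.** 30 women per arm; visits at baseline, 3 and 9 months; detectable effects of 0.8 SD (30 per arm) and 0.9 SD (after 20% attrition).

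**Assumptions, since the protocol gives no figures.** SD of 1 at every visit; the same correlation r between any two visits, from 0.3 to 0.9; two-sided alpha of 0.05; a true effect of 0.8 SD at both postpartum visits.

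**1. The protocol's own figures.** With a two-sample t-test, 0.8 SD at 30 per arm has 86% power. Twenty per cent attrition of 60 is 12 women, leaving 48, or 24 per arm; 0.9 SD at 24 per arm also has 86% power. The two effect sizes therefore agree with each other. The printed n=16 does not follow from 20% of 60; that is a separate slip and nothing below depends on it.

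**2. Between-group term with baseline as a level of time.**

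- Expected value: (0 + 0.8 + 0.8)/3 = 0.533, which is two thirds of 0.8.
- Variance of a woman's three-visit mean: (1 + 2r)/3. Variance of her two-visit postpartum mean: (1 + r)/2.
- Example at r = 0.5. Three visits: SE = √[(2/30)(0.667)] = 0.211, ratio 0.533/0.211 = 2.53. Postpartum only: SE = √[(2/30)(0.75)] = 0.224, ratio 0.8/0.224 = 3.58.

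**3. Change contrast against baseline adjustment.** Variances relative to the 9-month value alone (set to 1): change score 2(1 − r); ANCOVA 1 − r². Their ratio is (1 − r²)/[2(1 − r)] = (1 + r)/2.

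| r | change score | ANCOVA | ANCOVA/change |
|---|---|---|---|
| 0.3 | 1.40 | 0.91 | 0.65 |
| 0.5 | 1.00 | 0.75 | 0.75 |
| 0.7 | 0.60 | 0.51 | 0.85 |

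The change score beats the 9-month value alone only if 2(1 − r) < 1, that is, r > 0.5. The ratio (1 + r)/2 never exceeds 1, so apart from the small cost of estimating one slope the change score never beats ANCOVA.

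**4. Power at 0.8 SD, 30 per arm.**

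| Contrast | r = 0.3 | 0.5 | 0.7 | 0.9 |
|---|---|---|---|---|
| Between-group, three visits (estimates 0.533) | 79% | 70% | 62% | 56% |
| Mean of the two postpartum visits (estimates 0.80) | 97% | 94% | 91% | 88% |
| Group*time, (3 − 1)(2 − 1) = 2 df | 77% | 90% | 99% | >99% |
| 9-month change score | 73% | 86% | 98% | >99% |
| 9-month value alone | 86% | 86% | 86% | 86% |
| 9-month ANCOVA | 89% | 94% | 99% | >99% |

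**5. Missing visits under a complete-case ANOVA.** With 20% lost monotonely, 60 × 0.8 = 48 women remain, and the 3-month values of women lost after that visit are discarded. With 20% missing independently at each postpartum visit, 60 × 0.8 × 0.8 ≈ 38 remain.

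One dropout scenario was simulated (about 20% lost, depending on the 3-month value in one arm; 4,000 runs for each of r = 0.3, 0.5 and 0.7). Against a true 0.80, complete-case ANCOVA gave about 0.85, a likelihood fit to all available data gave 0.80, and the complete-case change score also gave 0.80. Baseline adjustment therefore needs to be combined with use of all available data.

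**The case against.** The strongest reply is that the protocol says less than a critic may read into it. Several stronger readings are tempting and are not supported.

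- *The whole analysis is diluted.* Only the between-group term can be, and only if baseline is a level of time, which is not stated. Group*time is undiluted, and section 2.3 prefers it.
- *A third-trimester change score is imposed on every outcome and biases it.* For weight loss the outcome section already sets the booking weight as reference, and section 4.2 takes the baseline OGTT from the record. For other outcomes the change contrast is unbiased under randomisation; what is lost is precision. The protocol gives no correlation from which to call third-trimester values poor predictors.
- *Incomplete cases are dropped.* This is inferred from the name of the method. SPSS can also fit a mixed model, sections 3.3 and 4.1 say collected data will be used, and missing-data rules may sit in a SAP that is not at hand.
- *ANOVA is the only method, even for binary outcomes.* Regression is also mentioned, and ANOVA is not assigned to binary outcomes specifically.
- *The section 2.3 statement is simply false.* Set against follow-up alone, it holds when r exceeds 0.5, and its immediate purpose is to justify a control group.

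Efficacy is also secondary here, and the protocol expects to detect only large differences.

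All of this stands as a limit on the point. It does not remove it. The section fixes a method rather than leaving it open, offers a between-group term as an effect estimate without saying which visits it covers, and relies on the result to plan the next trial.

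**Conclusion.** The point holds in a limited form. As named, the two ANOVA terms are a poor choice for producing an effect size to carry forward.

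The one-third shrinkage of the between-group term depends on baseline being a level of time and on equal effects at 3 and 9 months. Under those conditions, power at 0.8 SD is 56–79%, against 88–97% for the mean of the postpartum visits. For the group*time change contrast the cost is efficiency alone: baseline adjustment has 15–35% less variance for r between 0.3 and 0.7. The loss of women with a missing visit depends on a classical complete-case ANOVA being used.

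The correlations, equal SDs and dropout mechanism are assumptions. The ordering of ANCOVA over the change score does not depend on the value of r. The section 2.3 statement needs a qualification; nothing in the protocol shows that it must be withdrawn. The primary feasibility outcome is untouched, so this is a worthwhile correction and not a flaw that undermines the trial.

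**What to change.** In section 2.4 (Trial Statistics and Analysis) and the Study Synopsis, replace the ANOVA sentence for continuous outcomes with a linear mixed model, fitted in SPSS, of the 3- and 9-month values:

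- **Terms:** arm, visit, arm × visit, and the pre-randomisation value as covariate.
- **Covariate by outcome:** booking weight for weight, as the outcome section already implies; the recorded OGTT for glucose, as in section 4.2; the baseline-visit value otherwise.
- **Women included:** all randomised women with any postpartum value.
- **Effect estimate:** the adjusted 9-month mean difference with 95% CI, named as the figure carried to the definitive trial.
- **Binary outcomes,** such as more than 5% weight loss: the risk difference with 95% CI.

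In section 2.3, qualify the comparison: with equal SDs, group*time is more precise than a follow-up comparison only when the baseline/follow-up correlation exceeds 0.5.

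The cost is a change of wording and slightly more analysis work. No extra data, visits or software are needed.

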**4.3 Randomisation Procedures**

Participants will be randomised using a computer-generated random number table in blocks of 10. Randomisation will be supported by the Clinical Trials Unit. Double blinding is not possible because the participants will know if they receive an intervention or not. However, this potential source of bias will be considered in the analysis and would be eliminated in a definitive trial. In order to address attrition bias, participants in the control group will be provided with diabetes and health information at follow-up (after completion of measurements).

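### The adjusted analysis is defined by reference to a stratification that the randomisation section does not describe, and that section gives a single block size of 10 in an open two-hospital trial

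*Protocol*

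**What the plan says.** The synopsis and section 2.4 (Trial Statistics and Analysis) carry the same sentence on the efficacy outcomes: "Further regression analysis will be used to adjust for any potential confounding factors not factored into the stratification". It follows an analysis of variance with group and group-by-time terms, which lists neither hospital nor any stratum. Stratification is mentioned nowhere else in the protocol.

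Section 4.3 describes the allocation method: "Participants will be randomised using a computer-generated random number table in blocks of 10". It adds that the Clinical Trials Unit supports randomisation and that "Double blinding is not possible because the participants will know if they receive an intervention or not". It names no stratification factor.

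Section 3 sets the size and the sites: "A convenience sample of 60 women with current GDM, 30 in each arm will be recruited", and "Potential participants will be identified by the clinical team working at KCH and GSTT". One clinic "sees around 200 new patients with GDM a year"; the other trust sees 700.

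The CONSORT flowchart in section 2.3 describes a combined baseline and randomisation visit. Its list puts randomisation ahead of the questionnaires, anthropometry, blood pressure and blood sample.

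**The concern.** Stratification is fixed when the allocation list is generated, and a later analysis plan cannot add it. A sentence that sorts covariates by whether they were used in stratification therefore needs a stratified design behind it. Section 4.3 does not describe one, so a reader cannot tell which factors the rule leaves out or brings in. What remains is adjustment for any potential confounder, at 30 women per arm. Section 2.4 (Outcome Measures) lists many candidates among its additional data, including birth outcomes, which arise after randomisation. The wording does not exclude them.

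Two design consequences follow from section 4.3 as it stands. Hospital is not named as a stratifier or a covariate, although two sites with unequal caseloads recruit. And one block size is written into the protocol of a trial in which allocation becomes known, so the end of each block can be worked out by anyone who tracks allocations.

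The trial is meant to supply the effect size and standard deviation for a definitive trial. The randomisation procedure is itself one of the listed feasibility items. Both are reasons to settle the wording before recruitment.

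**Working it through.** The protocol gives no figure to reproduce here. The core is a comparison of sections, followed by two illustrations of size.

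**1. The sections side by side.** The synopsis and section 2.4 treat stratification as an existing feature of the design. Section 4.3 describes a random number table, blocks of 10 and support from the Clinical Trials Unit, with no factor named. The protocol's own sections do not agree, whatever an analysis plan may add.

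**2. Predictability with a fixed block of 10.** Inputs: block size 10, so b = 5 per arm in each block; 60 women, so 60/10 = 6 blocks. Assumption (worst case): the recruiter knows the block size and every earlier allocation.

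- Expected allocations certain in advance, per block: 2b/(b + 1) = 10/6 = 1.67. Over six blocks: 6 × 1.67 = 10 of 60, or 17%.
- Expected correct guesses per block when always guessing the arm that is behind: b + (4^b / C(2b, b) − 1)/2 = 5 + (1024/252 − 1)/2 = 5 + (4.063 − 1)/2 = 6.53 of 10, or about 65%. Pure chance would give 50%.

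Simulation of permuted blocks of 10 gives the same values (1.67 and 0.653).

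**3. Hospital balance without stratification.** Inputs: caseloads of 200 and 700 a year (section 3). Assumption: enrolment follows caseload. Expected number from the smaller hospital: 60 × 200/900 = 13.3, taken as 13.

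- The number of those 13 allocated to one arm is hypergeometric (60 women, 30 per arm, 13 drawn).
- P(9 or more) = 0.0759 + 0.0236 + 0.0046 + 0.0005 + 0.00002 = 0.1046. By symmetry, P(4 or fewer) is the same.
- P(9:4 or worse in either direction) = 2 × 0.1046 = 0.209, about 21%. Simulation with actual unstratified blocks of 10 also gives 0.21.
- For comparison, blocks of 10 within hospital would give these 13 women one full block (5:5) plus three more, so at worst 8:5. A 9:4 split could not occur.

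**4. What a 9:4 split would do.** The share of women from the smaller hospital would differ between arms by 9/30 − 4/30 = 5/30. If the hospitals differed by 0.5 SD on an outcome (assumed; the protocol gives no hospital effect), the unadjusted estimate would move by 5/30 × 0.5 = 0.083 SD. The standard error at 30 per arm is √(2/30) = 0.258 SD. The shift is about a third of one standard error.

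**The case against.** Several points on the other side are sound.

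- A reader might infer that randomisation has no strata. Section 4.3 is silent on the matter and does not deny them, and the Clinical Trials Unit may hold a specification that has them. The document supports only that no stratification is described.
- A reader might also infer that the rule is back to front, because it adjusts for everything except the stratifiers. That can be so only if strata exist. Even then, the sentence speaks of further regression, an additional step, and does not say that stratifiers are left out of the main model.
- Nor is it right to say that hospital cannot be controlled. The open wording would allow it as a covariate; it is just not named.
- A detailed covariate list is commonly left to the analysis plan, so its absence is no fault. This stands. What the analysis plan cannot cure is a protocol rule that points to a design feature the protocol does not describe.
- Chance imbalance by hospital is not bias, and step 4 shows that its effect would be modest even with a sizeable hospital difference. This stands.
- The predictability figures assume full knowledge of block size and past allocations. The protocol does not say that recruiters hold this tally, nor that they do not. The flowchart puts eligibility and written consent before randomisation, which limits the scope for selective enrolment. The figures are therefore an upper bound.

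**Conclusion.** The inconsistency is real and can be read directly from the text: the synopsis and section 2.4 depend on a stratification that section 4.3 does not describe. Left as it is, the adjustment rule has no defined content.

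The size is moderate. The 10 certain allocations and the 65% guess rate hold for a recruiter with complete information. The 21% chance of a 9:4 or worse split rests on enrolment following caseload, and it concerns precision. The sentence governs an additional analysis of secondary, preliminary-efficacy outcomes. Of the primary feasibility outcome, only the item on randomisation procedures is touched. The changes should be made because they are cheap and because these estimates are meant to inform the definitive trial.

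**What to change.** **Section 4.3.** State that randomisation is stratified by hospital, with varying block sizes not disclosed to recruiters, and that the Clinical Trials Unit releases each allocation only after baseline measures are complete. Reconcile the order of items at the baseline visit in the section 2.3 flowchart with this.

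**Synopsis and section 2.4 (Trial Statistics and Analysis).** Replace the sentence with: *Models for outcomes measured at baseline adjust for hospital and the baseline value (follow-up values as the response, baseline as a covariate and not also as a repeated measure); outcomes without a baseline adjust for hospital only where numbers allow; any further adjustment uses named pre-randomisation covariates as a sensitivity analysis.* The first bracket is needed because a group-by-time analysis of variance would normally carry baseline as a repeated measure, and using it twice would be a new error. The second clause is needed because incident type 2 diabetes, a later GDM pregnancy, breast feeding duration and infant growth have no baseline value.

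**If the sponsor does not stratify.** Delete the reference to stratification and keep hospital as a covariate.

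**Cost.** A small change to the randomisation specification, a few sentences of protocol text and slightly more analysis work.
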